## Abstract

**Introduction::**

The benefits of pulmonary rehabilitation (PR) on exercise capacity, health-related quality of life (HRQoL), and prevention of readmission post exacerbation in chronic respiratory diseases (CRD) are well established. However, accessibility to PR programmes is limited by PR programmes mostly being available through hospital clinics only. Utilizing existing workforce and infrastructure in private physiotherapy and exercise physiology practices may be a solution to increase access.

**Methods::**

A mixed-methods assessor-blinded randomized controlled feasibility trial will be conducted in two parts. First, the efficacy of a training programme for private practice (PP) physiotherapists and accredited exercise physiologists who have not previously provided PR will be evaluated. Participant knowledge, skills, and confidence to provide PR will be measured before and after the training and at three months follow-up. Secondly, patient participants with CRD will be randomly allocated to receive twice weekly PP PR for 8 weeks or usual care from their general practitioner (GP). Exercise capacity, HRQoL, and health status will be measured before and after PR. A purposive sample of clinician and patient participants will partake in semi-structured interviews at the study conclusion. Interviews will continue until data saturation is achieved.

**Discussion::**

This study will provide data on the feasibility of providing PR by physiotherapists and exercise physiologists in the PP setting. Provision of PR in the PP setting has the potential to increase access to this highly evidence-based intervention to improve outcomes for people with CRD.

## Introduction

### Background and rationale

Chronic respiratory diseases (CRD) are one of the leading causes of morbidity and mortality worldwide and account for a substantial healthcare expenditure (Vos *et al.*, 2020). Pulmonary rehabilitation (PR) is an exercise and education programme for people with CRDs that improves exercise capacity and health-related quality of life (HRQoL) (McCarthy *et al.*, 2015), as well as reducing hospital readmissions (Moore *et al.*, 2016). PR is a cost-effective intervention with a dominant incremental cost per quality-adjusted life year (Deloitte Access Economics, 2018). National and international guidelines recommend people with CRDs should undertake PR (Bolton *et al.*, 2013, Alison *et al.*, 2017, Rochester *et al.*, 2023).

Despite the effectiveness of PR, as little as 5–10% of eligible patients have access to a PR programme (NSW Agency for Clinical Innovation, 2010). Fewer still complete the programme and, therefore, do not achieve full benefits (Singh *et al.*, 2020). Accessibility to programmes is a key barrier to patients undertaking and completing PR. Accessibility encompasses issues around location, travel, timing of programmes, and waiting list times (Johnston *et al.*, 2011, Cox *et al.*, 2017). Alternative models of PR that overcome these barriers have been flagged as a research priority (Rochester *et al.*, 2015). There has been an emergence of alternative models of PR that aim to address barriers to PR, including telerehabilitation (Cox *et al.*, 2021) and home-based PR (Holland *et al.*, 2017). However, these two models involve either unsupervised or remote exercise sessions and are largely staffed by existing PR services staff. Models of PR that are provided outside of existing secondary care services are needed to expand the available trained workforce. Environmental factors were the most frequently referenced domain affecting PR referral, uptake, completion, and attendance, and these factors represent 37% of mapped barriers or enablers (Cox *et al.*, 2017).

Globally, most people with CRDs are managed in the primary care setting by their general practitioner (GP) (Levy *et al.*, 2006). Conversely, PR programmes are primarily conducted in hospital outpatient settings (Johnston *et al.*, 2011, Singh, 2020). These programmes operate with long waitlists and there are environmental barriers related to transport, parking, and accessibility for people with respiratory conditions. PR conducted in community settings has been shown to have similar efficacy to hospital-based programmes (McNamara *et al.*, 2016). However, in practice these programmes are often still staffed by hospital employed health professionals.

There is an untapped existing primary care workforce and infrastructure of private practice (PP) physiotherapists and accredited exercise physiologists (AEPs), professions that are accredited to provide PR in primary care. For example, Australian health workforce data show that only 28% of physiotherapists and 7% of AEPs, the key professions that deliver PR, work in the hospital sector (Department of Health, 2019, Exercise & Sports Science Australia, 2023). However, 93% of Australian PR programmes are provided by hospital employed staff (Johnston *et al.*, 2011) and in the UK, 94% of programmes are provided by public organizations (Singh, 2020). The majority of these allied health professionals work outside of the hospital sector, with 57% of Australian AEPs and 40% of physiotherapists working in PPs (Exercise & Sports Science Australia, 2015, Australian Physiotherapy Association, 2023). Due to the sheer number of private practitioners and practices, private clinics close to patients’ homes may increase accessibility of PR.

Despite a large workforce credentialed to deliver PR, there is currently no funding model to support PR in the PP setting in most countries. Recent position statements identify the gap in utilization of PP allied health professionals in the management of chronic disease, and call for an expansion of the funding to allow for physiotherapists and AEPs to deliver PR wholly within the PP setting (Exercise & Sports Science Australia, 2021, Lung Foundation Australia, 2022). There are multiple reasons for this gap, including funding, training, and facilities. Currently, private physiotherapists and AEPs in Australia operate on a fee for service model. There are no subsidies to fund a complete PR programme, meaning patients would need to have private health insurance or pay fees out-of-pockets. There is a need for evidence of feasibility and effectiveness of PR delivered in the PP setting to support calls for a policy change in funding.

To date, trials implementing PR in PP have not provided an intervention consistent with international PR guidelines (Bolton *et al.*, 2013, Alison *et al.*, 2017, Rochester *et al.*, 2023). These guidelines recommend that PR programmes be at least eight weeks duration, with a minimum of two supervised exercise sessions per week and one unsupervised session (Alison *et al.*, 2017). Casey *et al.* (2013) conducted a large randomized controlled trial (RCT) comparing once weekly PR in primary care to usual care of no PR. The study showed a statistically but not clinically significant between-group improvement in HRQoL in favour of the PR group but no difference in exercise capacity (Casey *et al.*, 2013). The reduced frequency of PR in the intervention compared to national (Alison *et al.*, 2017) and international guidelines (Bolton *et al.*, 2013) may have contributed to this result. There have been smaller studies conducted, however, they also failed to meet guidelines (Zakrisson *et al.*, 2011, Anastasaki *et al.*, 2019) or were not conducted solely in primary care (Cecins *et al.*, 2017). It is also important to understand the upskilling required for physiotherapists and exercise physiologists to provide PR in primary care. In a systematic review on educational interventions for healthcare professionals for chronic obstructive pulmonary disease (COPD) management in primary care, only one RCT in this review evaluated education for physiotherapists or exercise physiologists providing COPD management, with no specific education on the provision of PR (Cross *et al.*, 2022), indicating a gap in the literature about upskilling physiotherapists and AEPs in this area of practice.

The current study seeks to bridge these knowledge gaps and examine whether it is feasible to provide an evidence-based PR programme provided by physiotherapist or AEPs in their PPs. It is also vital to gather data for the Australian-specific context. There is a critical need to determine how PR can be implemented more widely for people with CRD so that they benefit from the well-established and multidimensional improvements.

## Objectives

Part One: The primary objective is to investigate the efficacy of a PR training programme for PP physiotherapists and AEPs to develop the knowledge, skills, and confidence necessary to conduct a PR programme. The secondary objective is to identify if the training programme meets the needs of the PP clinician participants and is acceptable to them.

Part Two: The primary objective is to investigate whether it is feasible for PP physiotherapists and AEPs to conduct PR in primary care. Secondary objectives are: (i) to assess, in participants with CRD whether PR conducted in primary care improves exercise capacity, HRQoL, and health status compared to usual medical care provided by a GP; (ii) to investigate whether the delivery of PR is acceptable from the perspective of PP physiotherapists and AEPs; and (iii) to provide data to allow for the design of a full-scale definitive trial.

We hypothesize that after appropriate upskilling of clinicians, PR provided in primary care will be acceptable to PP clinicians and patients, feasible to implement, and will be associated with increased exercise capacity and HRQoL in people with CRD when compared to usual care.

## Methods and analysis

### Participants, interventions, and outcomes

#### Trial design

The study will be a mixed-methods assessor-blinded randomized controlled feasibility trial, conducted in two phases. Part One will involve training clinician participants in PR and Part Two will involve a randomized controlled trial of PR delivered to patient participants by those clinicians upskilled in Part One compared to usual care.

#### Participant timeline

A timeline for participants in both parts of the study is outlined in Figure 1.

**Figure 1. f1:**
[figure not shown]
Part One and Two participant timelines. Abbreviations: COPD, chronic obstructive pulmonary disease; ILD, interstitial lung disease; OPD, outpatient department; PR, pulmonary rehabilitation; mMRC, modified Medical Research Council dyspnoea scale; 6MWT, six-minute walk test; ISWT, incremental shuttle walk test; 1mSTS, 1-minute sit-to-stand; SGRQ, St George Respiratory Questionnaire; CAT, COPD Assessment Test; PP, private practice; GP, General Practitioner; GRCQ, Global Rating of Change Questionnaire.

#### Study setting

The study will be conducted within the geographical area of three local health districts (LHDs) in metropolitan Sydney, Australia. Patient participant assessments and intervention will be conducted wholly within the participating physiotherapy or AEP practices.

#### Participants

Clinician participants will be recruited for Part One and patient participants recruited for Part Two. The inclusion and exclusion criteria for both participant groups are outlined in Table 1.

**Table 1. tbl1:** Inclusion and exclusion criteria for clinician and patient participant groups

	Clinician participants	Patient participants
Inclusion criteria	- Registered physiotherapist or accredited exercise physiologist - Working in private practice where: o At least two staff (clinical or administrative) are present during assessments and group exercise sessions o There is adequate space for group exercise for a minimum 3 participants o There is at least 10m straight distance to perform a field walking test o Accessible for people with chronic respiratory disease - Willing to provide intervention for part two of study (twice weekly PR for 8 weeks) - Have or be willing to obtain current CPR training prior to assessing any study participants	- Age >18 years - Diagnosis of COPD or ILD (confirmed with spirometry (Williams *et al.,* 2014) or diagnosis by medical doctor) - Referred to pulmonary rehabilitation at one of three metropolitan LHD hospitals and on the waitlist - Willing to attend twice weekly PR for 8 weeks in a private practice setting
Exclusion criteria	- Physiotherapists or AEPs with significant prior PR experience (e.g. more than one rotation as Level 1 physiotherapist or AEP in a hospital PR setting or delivery of Lungs in Action) - Physiotherapists or AEPs with postgraduate cardio-pulmonary qualifications	- Exacerbation of respiratory disease within 4 weeks prior to recruitment - Completed PR in the past year - Prescribed home supplemental oxygen or requiring supplemental oxygen for exercise (desaturates < 80% SpO_2_ on field walking test) - Medical conditions that contraindicate safe group exercise outside hospital setting (e.g. unstable cardiac disease, severe musculoskeletal impairments) - Unable to provide informed consent

Abbreviations: PR, pulmonary rehabilitation; CPR, cardio-pulmonary resuscitation; AEP, accredited exercise physiologist; COPD, chronic obstructive pulmonary disease; ILD, interstitial lung disease; LHD, local health district; SpO_2_, oxygen saturation measured by pulse oximetry.

### Recruitment

Clinician participants will be recruited from study advertisements through primary health network newsletters, professional societies, and contact with PR services. Patient participants will be recruited from waitlists of existing PR services within the participating LHDs. Potential participants will be screened for eligibility from existing service waitlists by a member of the treating clinical team. Eligible participants will be contacted by the researcher.

#### Randomization, allocation, and blinding procedures

Patient participants will be randomized 1:1 to either receive the intervention or usual care. Randomization will be conducted within the randomization module of REDCap and be performed by an unblinded member of the research team. Randomization will be stratified by exercise capacity (6-minute walk distance (6MWD) ≥350m or <350m, ISWT ≥250m or <250m), and level of breathlessness with activity (modified Medical Research Council dyspnoea scale (mMRC) ≥3 or <3).

For Visit 1, clinical outcome measures will be completed by PP physiotherapists or AEPs. Randomization will occur after completion of Visit 1 data collection. The study coordinator will remain blinded to group allocation throughout the trial and will perform assessments at Visit 2. Due to the nature of the intervention, both clinician and patient participants will not be blinded to group allocation. Data will be analysed without knowledge of group allocation.

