##### Part two

Data will be analysed in accordance with CONSORT extension for randomized pilot and feasibility trials guidelines. Intention-to-treat analysis will be used. Feasibility outcomes will be described using proportions and corresponding 95% confidence intervals (CI), or for continuous variables means, standard deviations, and ranges. The proportion of missing data will be summarized for each clinical outcome at each time point. Where possible, reasons for missing data will be recorded. Descriptive statistics will summarize clinical outcomes and effect sizes estimated. Completion rates, missing data, variances, difference, and 95% CIs pre- and post-intervention as well as between-group differences will be calculated. Change data for field walking tests will be presented as percentage changes. The proportion of participants who meet the minimum clinically important differences for each test will be calculated. For all other clinical outcomes, change data will be presented as absolute changes.

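### Walking and sit-to-stand tests change assessor between Visit 1 and Visit 2 in every patient, so within-arm pre-post differences and MCID proportions cannot separate patient change from assessor change

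*Protocol article*

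**What the plan says.** The Protocol article, section Randomization, allocation, and blinding procedures, assigns the two visits to different people. For baseline, "For Visit 1, clinical outcome measures will be completed by PP physiotherapists or AEPs". For follow-up, "The study coordinator will remain blinded to group allocation throughout the trial and will perform assessments at Visit 2". The order of events is also fixed: "Randomization will occur after completion of Visit 1 data collection".

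The baseline assessors are new to this work by design. Trial design describes "PR delivered to patient participants by those clinicians upskilled in Part One compared to usual care". Table 1 excludes "Physiotherapists or AEPs with significant prior PR experience" and confirms that these clinicians test patients, through the inclusion criterion "Have or be willing to obtain current CPR training prior to assessing any study participants".

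Quantitative data analysis, Part two, plans descriptive summaries and effect sizes, and then states that "difference, and 95% CIs pre- and post-intervention as well as between-group differences will be calculated". It adds that "The proportion of participants who meet the minimum clinically important differences for each test will be calculated". Walking-test change is to be shown as a percentage and other outcomes as absolute change.

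Two safeguards are stated. Interventions, Part one, requires proficiency in three of four components for each exercise test and also in that test's core competencies. Outcomes, Part two, requires the walking tests to follow the ERS/ATS technical standards and each patient to keep the same test throughout. Neither safeguard keeps the assessor the same, and the limitations in the Discussion do not mention the switch.

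**The concern.** Field walking tests and the sit-to-stand test depend to some degree on how they are instructed, encouraged and timed. Here every Visit 1 result comes from one of several recently trained practice clinicians and every Visit 2 result from the coordinator. Within an arm, a change in the patient and a change in how the test is run both appear as the same pre-post difference, and no within-arm analysis can split them. The confidence interval does not help, because it reflects sampling error and not a systematic shift.

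Three planned outputs are exposed: the pre-post mean with its interval, the MCID proportion, and the SD of change that would inform the definitive trial. Outcomes, Part two, says the clinical measures will test effectiveness, so a reader of the results could take the first two as the effect of rehabilitation.

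**Working it through.** **Sample size behind the intervals.** Sample size gives 30 per arm and 20% attrition: 30 / (1 - 0.20) = 37.5, rounded up to 38 per arm, and 2 x 38 = 76. This reproduces the stated total, which is not in dispute. The 30 completers per arm are used below.

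**Model.** Let observed change = true change + b, where b is a systematic assessor shift common to both arms. Work in units of the SD of change and assume normality with equal SD in both arms.
- Pre-post mean in an arm = true mean + b.
- Between-arm mean difference = (mean PR + b) - (mean control + b) = mean PR - mean control, so b cancels.
- MCID proportion = 1 - Phi(MCID - true mean - b), so b does not cancel within an arm.

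**Assumptions.** The document gives no size for b, the true change or the MCID in SD units. The range taken for b is -0.5 to +0.5 SD, with a true mean of 0.5 SD (PR) and 0 (control) and an MCID of 0.5 SD.

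| b | Pre-post mean, PR | Pre-post mean, control | Between-arm mean difference | MCID, PR | MCID, control | Difference in points |
|---|---|---|---|---|---|---|
| -0.50 | 0.00 | -0.50 | 0.50 | 30.9% | 15.9% | 15.0 |
| -0.25 | 0.25 | -0.25 | 0.50 | 40.1% | 22.7% | 17.5 |
| 0 | 0.50 | 0.00 | 0.50 | 50.0% | 30.9% | 19.1 |
| +0.25 | 0.75 | 0.25 | 0.50 | 59.9% | 40.1% | 19.7 |
| +0.50 | 1.00 | 0.50 | 0.50 | 69.1% | 50.0% | 19.1 |

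(Differences are taken before rounding.)

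**A less favourable case for the MCID contrast.** With a true PR mean of 1.0 SD and an MCID of 1.0 SD, the PR proportion again runs from 30.9% to 69.1% (true 50.0%). The between-arm difference runs from 24.2 to 38.3 points (34.1 with no shift). The contrast is steadier than the within-arm figure but not immune. If there is no treatment effect, the two proportions are equal at every b and their difference is zero.

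**Against sampling error.** The half-width of a 95% CI for a pre-post mean at n = 30 is t(0.975, 29) / sqrt(30) = 0.37 SD. A shift of that size would equal the sampling error, and the interval would not show it.

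**On the percentage scale planned for walking tests.** Observed change = (1 + true) / (1 + e) - 1, where e is the proportional error at Visit 1. With e = -5%, a true 0% becomes 1.00/0.95 - 1 = +5.3% and a true +10% becomes 1.10/0.95 - 1 = +15.8%. With e = +5%, they become -4.8% and +4.8%. At e = -5% the between-arm difference goes from 10 to 10.5 points: a slight rescaling, with no shift away from zero when there is no effect.

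**SD of change.** A constant shift adds no variance. Only variation among Visit 1 clinicians does. If that variation has SD s, as a fraction of the SD of change without it, the variance rises by a factor of 1 + s^2. The document gives no value for s.

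**The case against.** The case on the other side is substantial, and much of it stands.

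- **No within-arm efficacy claim is planned.** Objectives frames the clinical effect, and the hypothesis, against usual care. The analysis section calls the clinical summaries descriptive, and the Discussion says the trial is not powered for effectiveness. Uncontrolled pre-post change also carries learning and regression to the mean, which is why there is a control arm. This limits the point to how the within-arm figures are labelled and which figures carry the effect statement. It does not remove it, because intervals and MCID proportions are still planned.
- **The safeguards are real.** Core-competency proficiency and the ERS/ATS standards may make any shift small. They do not show that it is zero.
- **Clinician testing at baseline has a purpose.** It is what the clinicians are trained for, and it feeds the exercise prescription. The follow-up assessor has to differ because the clinicians are unblinded. Blinding does not force a different assessor at Visit 1, since randomization comes afterwards, but there is good reason to leave baseline testing with the clinicians.
- **The size is assumed throughout.** That is correct, and the shift could go in either direction.
- **The SD argument is conditional.** If the definitive trial keeps baseline testing by practice clinicians, the observed SD of change is the relevant one. This stands, and it is why both SDs should be reported and neither discarded.

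A reader might infer that the switch biases the randomized comparison or undermines assessor blinding. The document does not support that: both arms go through the same change of assessor, Visit 1 precedes allocation, and Visit 2 is blinded. Nor does it support the inference that the baseline tests are inaccurate.

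**Conclusion.** The point holds for the performance tests and for within-arm results only. Assessor and visit are completely confounded, so the planned pre-post differences with their 95% CIs, and the MCID proportions, cannot be read as change in the patient alone. Under the assumed range of ±0.5 SD, the rehabilitation arm's MCID proportion could lie anywhere from 31% to 69% when the truth is 50%. That range shows sensitivity; it is not an estimate of any actual shift.

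The between-arm mean difference is not biased by a common additive shift, and a proportional baseline error only rescales a percentage difference slightly. The between-arm difference in MCID proportions is much less sensitive than either proportion alone. The primary outcome, attendance at 12 of 16 sessions, is unaffected. The SGRQ, CAT and mMRC are less exposed because the result depends less on how an assessor runs a test. It would go too far to say that every pre-post change in the trial is compromised, or that the SD of change is known to be inflated.

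**What to change.** Amend Quantitative data analysis, Part two, as follows.

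1. Base every statement about the effect of rehabilitation on the between-arm contrast.
2. Report MCID attainment as the between-arm difference in proportions with its 95% CI. The proportion in each arm may be shown beside it.
3. Keep within-arm pre-post results as descriptive only, and state that for the walking and sit-to-stand tests they include the change of assessor.
4. For the definitive trial's design, report the SD of Visit 2 values by arm beside the SD of change, noting that the latter may include variation among Visit 1 assessors.

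Do not have the coordinator test Visit 1 at only some practices. That would give some patients one assessor and others two, turning a uniform shift into a mixture and adding variance to change.

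The cost is analysis and reporting wording, with no new data and no change to trial conduct. The downside is that no stand-alone within-arm improvement can be claimed.
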